# Study PROTOCOL

---

## ADMINISTRATIVE INFORMATION

### 1.0 Title

Vaping in At-risk Populations: Effects on Mental and Physical Health (VAPE) Study: A Patient Perspective

### 2.0 Protocol version

Date and version: Version 1, September 30, 2020

### 3.0 Sources of funding,

This study is funded by Canadian Institutes for Health Research, HEV-172884 .

### 4.0 Study Team Roles and Responsibilities

Table 1 below shows the study team members and their specific roles in the study.

## 5.0 INTRODUCTION

### 5.1 Background and Rationale

Vaping has gained popularity in Canadians, particularly in youth and young adults. Accordingly, many questions have been raised about the short- and long-term health outcomes given the scarcity of current evidence. Regarded by some as an alternative to combustible cigarettes, evidence suggests that vaping and e-cigarettes are not as innocuous as this perspective may imply. The use of these products results in the release of harmful toxins that pose important risks to the user, as well as to the recipients of second- and third-hand smoking. However, little research has investigated the short- and long-term effects that vaping may have on mental and physical health vulnerabilities. This lack of data is met with an even greater uncertainty of the effects of vaping cannabis products, the investigation of which is made especially important by the recent legalization of cannabis. Research is needed to investigate short and long-term health outcomes of vaping in vulnerable populations, specifically in those receiving out-patient treatment for opioid use disorders (OUD) who commonly use multiple substances, which may complicate or influence opioid treatment outcomes in these patients.

The number of individuals between the ages of 16 and 19 who report ever having vaped increased from 29.3% to 37.0% between 2017 and 2018, with a corresponding increase in number of days vaped in the same time. While proponents of vaping might suggest increases can be explained by increased uptake of vaping as a substitution for cigarettes in an attempt to quit smoking, evidence indicates that the upward trend in vaping is observed most strongly among those who identify as “never” or “experimental” smokers. As vaping substances such as nicotine or cannabis retains their addictive properties, this behaviour presents a concern for at-risk populations, including those with OUD.

OUD is a serious, chronic, relapsing and remitting characterised, at times, by compulsive use of opioids, and sustained behavioural changes affecting the individual's life and functioning. OUD leads to deleterious consequences to individuals and society, including increased likelihood for infections such as hepatitis and HIV, psychiatric comorbidities, social adverse consequences, and increased mortality. Canada is the world's second largest opioid consumer globally and the increased availability of prescribed opioids has contributed to diversion and, in turn, the

current opioid epidemic. Patients with OUD are at greater risk of polysubstance use, as well as physical and mental health co-morbidities. Both cigarette smoking and cannabis use are highly prevalent in this population and it remains important to examine the impact of vaping on these patients. OUD may also pose a respiratory risk due to the depressive effects of opioids on the respiratory system and additional substance use through insufflation and inhalation, potentially putting these individuals at higher risk of infection and death from the novel COVID-19. Research has suggested that vaping may be associated with respiratory health conditions including chronic obstructive pulmonary disease (COPD) and wheezing. The CDC has termed any respiratory condition related to vaping as e-cigarette or vaping product-use associated lung injury (EVALI). EVALI includes any shortness of breath, lung infection, fever, etc. related to vaping. As of January 2020, over 2,700 cases of EVALI have presented in the United States.

Recent research suggests that those who vape may be at increased risk for COVID-19 infection and its more severe consequences. The symptomology associated with COVID-19 includes shortness of breath, fever, and cough, which can lead to pneumonia and acute hypoxemic respiratory failure. There are concerns that smokers, which include those who vape, may develop serious complications if they contract COVID-19. Individuals may also contract COVID-19 through the sharing of vape devices as the coronavirus may remain active on aerosols (and associated surfaces) from several hours to days. Additionally, individuals with OUD are also at higher risk of deleterious consequences of COVID-19.

Vaping has also been associated with psychological and mental health concerns. In a study of university students, the use of e-cigarettes (devices that turns liquid containing nicotine into vapor) was found to be associated with multi-drug use, including alcohol and opioids, low self-esteem, symptoms of attention-deficit/hyperactivity disorder, post-traumatic stress disorder, gambling disorder, and anxiety. E-cigarette use was associated with traits of impulsivity and internalizing and externalizing problems. There is likely a bidirectional association between vaping and mental health. Studies showed higher depression and stress scores were predictive of e-cigarette use in college students. These findings highlight the co-occurrence of vaping with mental health challenges and problematic substance use in non-psychiatric populations. Further, these studies highlight the need for investigating vaping behaviour in a high-risk population, and specifically in the context of the opioid epidemic within the current COVID-19 pandemic where vulnerable groups are expected to bear the brunt of the epidemic within the pandemic.

We completed a systematic review of vaping within OUD population and found that some research has suggested that vaping may be associated with adverse outcomes including increased psychiatric distress and physical health symptoms such as coughing and headaches. However, there is no research examining vaping and COVID-19 related symptoms in the OUD population.

Preliminary data from our study investigating pharmacogenetics of OUD in patients receiving medication-assisted treatment (MAT) (POST study, a CIHR funded cohort study, n=2,360, individuals 16 years and older, 56% men) showed 19.2% of individuals with OUD use vaping, with 74% of participants vaping nicotine, 33% vaping cannabis (THC, CBD, Marijuana and shatter), 11% vaping of both cannabis and nicotine, and 5.5% reporting vaping water or “flavour”. The POST Study collected information pertaining to initiation of opioid use, opioid addiction treatment history, cannabis use, illicit drug use, and physical and mental health symptoms, using a set of questions and validated clinical questionnaires. Specific information pertaining to vaping behaviour has also been collected. Participants were asked

about vaping status (binary variable), and the type of substance that they vape (free-text response). Table 1 describes demographic characteristics and vaping behaviours in a subset of the POST study who reported “yes” to vaping (n=453), stratified by sex.

Further data are needed to understand individuals’ perceptions and motivations for vaping in the OUD population. Additionally, given the variability of substance use outcomes in those receiving treatment, it is also important to explore if other substance use (i.e., cocaine, opioids, cannabis, amphetamines and benzodiazepine use) also differ in those that vape and have OUD.

## **6.1 Study Objectives**

The primary objective of this qualitative study is to understand the perceptions and motivations for vaping in the OUD population receiving medication assisted treatment. The secondary objective is to collect specific information pertaining to frequency of use, amount, and vaping substance as well as co-substance use information.

## **7.0 Study Methods**

We will conduct qualitative interviews on the phone to obtain information on the perceptions of vaping and vaping behaviour patterns (i.e., reasons for vaping, type of substance, effect of vaping on health) in the OUD population. With the expertise of a qualitative expert, we have designed an unstructured interview guide (see attached interview guide) that have 8 broad, open-ended questions that will allow the interviews flexibility of asking more tailored questions as the participant shares their thoughts and experiences. The qualitative interviews will be audio recorded and transcribed without any identifying information.

In addition to the qualitative interview, we will also administer a Questionnaire of Vaping Craving (QVC), a short validated questionnaire for assessing vaping beliefs and behaviours, and collect demographic details. We will also be collecting urine drug screen results for opioids, cocaine, amphetamines, cannabis and benzodiazepines from medical records for a period of 12 months after study enrolment.

Participants will be provided with a \$10.00 Tim Hortons gift card for their participation.

## **8.0 Study Setting**

We will recruit 50 participants attending medication assisted treatment clinics through the Canadian Addiction Treatment Centre (CATC).

## **9.1 Eligibility Criteria**

1. People aged 16 years or older
2. Fulfil DSM-5 criteria for OUD
3. Receiving medication assisted treatment for OUD
4. Currently vape
5. Able to provide informed consent

## **9.2 Research Personnel conducting qualitative interviews**

All research assistants involved in conducting the qualitative interviews will be trained by [name].

## **10.0 Outcomes**

### **Primary Outcome Measures**

As the primary aim is to collect information on perceptions of vaping and will be collected through a qualitative interview, there is no structural outcome. This information will be open ended and collected through the interview guide developed.

### **Secondary Outcome Measures**

Our **secondary outcome** is Questionnaire of Vaping Craving (QVC). This will be administered to participants electronically after the qualitative interview. We will also get information relating to co-substance use for a period of 12 months after study enrolment using their medical records at CATC.

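### Cannabis is treated as a co-used substance although about a third of vapers vape cannabis, so the cannabis screen does not cleanly measure use alongside vaping

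*Protocol*

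**What the plan says.** Section 6.1 pairs two things in the secondary objective: vaping frequency, amount and substance, and co-substance use. The vaped substance is asked about in the telephone interview (Section 7.0).

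Co-substance use comes from clinic records. Section 7.0 plans to collect "urine drug screen results for opioids, cocaine, amphetamines, cannabis and benzodiazepines from medical records for a period of 12 months after study enrolment", and Section 10.0 states: "We will also get information relating to co-substance use for a period of 12 months after study enrolment using their medical records at CATC". The last paragraph of Section 5.1 lists cannabis, with cocaine, opioids, amphetamines and benzodiazepines, as other substance use to be explored in people with opioid use disorder who vape.

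The same section describes what vapers in the preliminary cohort vape: "33% vaping cannabis (THC, CBD, Marijuana and shatter), 11% vaping of both cannabis and nicotine". Section 9.1 requires current vaping but does not restrict the substance, so cannabis vapers are eligible.

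Section 16.0 plans linear or logistic regressions relating socio-demographic variables to the substance use outcomes. It does not name the vaped substance as a covariate or stratum.

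**The concern.** Cannabis stands on both sides of the comparison. For some participants it is the substance they vape; for all participants it is also on the list of other substances. A positive screen does not show whether the cannabis was vaped or taken another way.

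In someone who vapes only nicotine, a positive cannabis screen is evidence of a second substance. In someone who vapes only cannabis, the same result may be the vaping that made the person eligible. If the two are pooled, the cannabis rate mixes co-use with vaping. A regression on socio-demographic variables would then partly describe who vapes cannabis rather than who uses cannabis in addition to vaping.

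Timing adds a smaller point. Vaping is described as recorded at one interview, and no repeat assessment is planned. The screens cover only the year that follows, and no earlier screens are taken as a baseline. The result is substance use after enrolment, and should be named so.

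**Working it through.** **Inputs from the protocol**
- Preliminary cohort of 2,360, of whom 19.2% vape; 453 vapers (Section 5.1).
- Among vapers: 74% nicotine, 33% cannabis, 11% both, 5.5% water or flavour (Section 5.1).
- Planned sample: 50 (Section 11.0).

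**Step 1. Reproduce the plan's figure.** 2,360 × 0.192 = 453.1, against the stated 453. It reproduces.

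**Step 2. Does the 33% include the 11%?** 74 + 33 = 107, already above 100, so the nicotine and cannabis figures must overlap. Subtracting the dual vapers gives 74 + 33 − 11 = 96; adding 5.5 gives 101.5, close to 100 allowing for rounding or a small further overlap. So the 33% is any cannabis, and 33 − 11 = 22% vape cannabis without nicotine.

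**Step 3. Expected numbers among 50**, assuming the sample resembles the preliminary cohort.
- Any cannabis: 50 × 0.33 = 16.5 (binomial 95% range 10 to 23).
- Cannabis without nicotine: 50 × 0.22 = 11.
- Both: 50 × 0.11 = 5.5.

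**Step 4. Effect on the cannabis rate.** Let c be the proportion with a positive cannabis screen among those who do not vape cannabis. The protocol gives no such figure, so c is assumed at 10%, 30% and 50%. As an upper limit, suppose every cannabis vaper screens positive.
- Pooled rate = 0.33 + 0.67c.
- Rate leaving out those who vape cannabis without nicotine = (5.5 + 33.5c) / 39, where 33.5 = 50 × 0.67 and 39 = 50 − 11.

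| c (assumed) | Pooled rate | Without the 11 | Non-cannabis vapers only |
|---|---|---|---|
| 10% | 39.7% | 22.7% | 10% |
| 30% | 53.1% | 39.9% | 30% |
| 50% | 66.5% | 57.1% | 50% |

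In the pooled column, 33 percentage points come from cannabis vapers whatever the value of c, and 22 of those from people who vape it without nicotine. These are ceilings. The 33% includes people who named CBD, and the protocol does not say whether they would screen positive.

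**Step 5. How far the window departs from the vaping described.** If a fraction q stops vaping at a constant rate over the year, the share of person-time still concurrent with vaping is q / (−ln(1 − q)). With q assumed at 10%, 30% and 50%, this is 94.9%, 84.1% and 72.1%. Even at the high end, most of the window would overlap with vaping, so the timing point is one of naming and baseline, not a failure of the design.

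**The case against.** The strongest reply is that the protocol contains no co-use score. It lists screen results to be collected and calls them substance use outcomes; how they are derived may be set out in an analysis plan that is not shown. The vaped substance is recorded for each person, so cannabis vapers can be identified later without any change of design. This stands as far as it goes: the data permit the repair. But the protocol itself classes cannabis as other substance use and applies the co-substance label without qualification, while reporting that a third of vapers vape it.

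It is also fair to say that the 16 to 17 participants are not all misclassified. About 5.5 vape both products, and for them cannabis beside nicotine is ordinary co-use. Cannabis vapers may also use cannabis by other routes; Section 5.1 calls its use highly prevalent in this population. This too stands, and narrows the clearest problem to about 11 of 50.

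Three stronger readings are tempting, and the protocol does not support them.
- **The forward window fails to measure co-use.** Section 6.1 sets no time frame, participants vape at entry, early screens fall near the interview, and the planned regression does not relate the screens to vaping. A forward window is a defensible follow-up. Leaving treatment could thin it, but the protocol gives no retention figure, and leavers keep the screens already taken.
- **Opioid screens would be positive because of prescribed treatment.** Section 9.1 does require "Receiving medication assisted treatment for OUD", but nothing says that the opioid screen detects the prescribed medication.
- **A look-back should be the primary window.** No measurement of vaping is tied to the earlier months either, and patients new to treatment have little history.

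**Conclusion.** The point holds for cannabis only. The protocol treats cannabis as a co-used substance although about a third of vapers in its own data vape it, and the screen cannot separate the two uses. The cannabis result does not cleanly measure use alongside vaping. A reader might infer that the co-substance outcome as a whole fails to measure co-use; that goes too far, because the overlap does not reach the cocaine, amphetamine or benzodiazepine results.

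The expected size is 16.5 of 50 participants, about 11 of whom vape cannabis without nicotine. Cannabis vapers could contribute up to 33 percentage points to the pooled cannabis rate. This rests on two assumptions: that the sample resembles the preliminary cohort, and, for the ceiling, that all cannabis vapers screen positive.

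The matter concerns supplementary data in a study whose primary aim is qualitative. It is still worth correcting, because the split costs nothing in data and changes what the cannabis result can be said to show.

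**What to change.** 1. Using the vaped substance recorded at interview, report and model cannabis screens separately for participants who do and do not vape cannabis. Do not count a cannabis-positive screen as co-use in those who vape only cannabis. This needs no new data. Its cost is precision: the cannabis-vaping group would number about 16 to 17, so any model within it would be imprecise and should be read as descriptive.
2. In Sections 7.0 and 10.0, describe the 12-month result as substance use after enrolment. This is a change of wording only.
3. Keep the 12-month window and, as an optional addition, take from the same records the screens shortly before or at the interview as a baseline. This costs consent wording for the earlier records, a report to the ethics board before implementation (Section 21.0) and a slightly longer record pull. Patients new to treatment will have a short history, which should be stated with the results.

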## **11.0 Sample size**

Based on the qualitative literature, it has been suggested that one should only conduct qualitative interviews to the point of saturation, that is until no longer obtaining different perspectives. It has been suggested that for observational studies, between 30-50 participants is the recommendation. The sample size for this study is 50 participants.

## **12.0 Recruitment**

We will recruit from Canadian Addiction Treatment Centres. We will provide the centers with a poster announcement to place in the clinic with the study details and contact information. The Director of Operations will be giving us a list of 3 sites that we will recruit from. Once a site has reached saturation, we will be provided with another site. At any given time, the maximum number of sites that will have ongoing recruiting will be 3. We have provided a template for this poster under recruitment material.

## **13.0 Blinding**

This study is qualitative interview therefore is not possible for participants to be blinded.

## **14.0 Data Collection Methods**

A specifically designed case report forms (CRF) will be used to collect the data using electronic research data capture, REDCap. We will be using REDCap to electronically store the surveys containing the outcome instruments. We will be using the phone to conduct the qualitative interviews. The recorded phone interviews will also be stored on REDCap. The recorded interviews will be kept for 10 years and then safely destroyed.

### **15.0 Data Management**

Data will be entered into research Electronic Data Capture (REDCap) (<http://project-redcap.org/>). Electronic data will be hosted in the local institution server at McMaster Mac or Joes? with passcode protection and electronic security measures in keeping with institutional policy and privacy regulations. Reports will be generated weekly to check data quality and recruitment progress.

### **16.0 Statistical analyses**

Data for this aim will be analyzed using Nvivo 12 qualitative data analysis software (QSR International). The free-text data will be run through a word frequency query to logically arrange the information and determine the most common words. The word count query will help identify initial patterns in the data; there is evidence that this function improves analytic accuracy when compared to manual qualitative word frequency analyses.

In order to avoid decontextualization of the free-text answers, the minimum number of letters permissible in the word frequency query will be set to four. Any word with a frequency weighting of greater than 0.5% will be coded as a node. A node is a collection of references found in the free-text data that corresponds to a particular theme or word. Words with a word frequency percentage above 0.5% that are related to a similar theme will be grouped in the same node. From this output, we will employ matrix coding queries. The output of a matrix coding query is a chart that displays the number of references coded at each node and the corresponding demographic attributes for each participant.

The thematic data will be presented for the overall population, by sex, gender, type of MAT, age, and ethnicity.

Additionally, with the urine drug screen results from the medical records, we will conduct linear and logistic regressions to see if there are any differences between socio-demographic variables and substance use outcomes in this population. We will need to see the distribution of the outcomes to decide on whether a linear or logistic model will be appropriate.

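### The four-letter minimum in the word frequency query shuts out THC and CBD, so cannabis mentions are undercounted in the nodes and matrices

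*Protocol*

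**What the plan says.** Protocol section 16.0 describes one route from interview text to results:

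- **Filter.** To avoid decontextualization, "the minimum number of letters permissible in the word frequency query will be set to four".
- **Node rule.** "Any word with a frequency weighting of greater than 0.5% will be coded as a node".
- **Grouping.** "Words with a word frequency percentage above 0.5% that are related to a similar theme will be grouped in the same node".
- **Matrix step.** "From this output, we will employ matrix coding queries". The resulting chart "displays the number of references coded at each node", set against participants' demographic attributes.

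The section gives no exception list, synonym list or recoding of abbreviations.

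Two other places bear on this. Section 5.1 summarises the substances named by people who vape in the team's earlier cohort, including "33% vaping cannabis (THC, CBD, Marijuana and shatter". Section 6.1 puts "frequency of use, amount, and vaping substance" in the secondary objective, and section 7.0 lists the type of substance among the topics of the interview.

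**The concern.** A length filter is normally used to remove function words that carry little content. Here it also removes two substance names that the team has already met in this kind of population. The nodes and the matrix tables come from the query's output, so a word lost at the filter is lost at every later step described.

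Two things are at stake. First, counts for cannabis would be too low if participants say THC or CBD. Second, THC and CBD could not be shown as distinct products in any table by participant characteristics. Section 5.1 describes the evidence on vaping cannabis products as even thinner than that on vaping generally, so the loss falls on a topic that the rationale singles out.

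**Working it through.** **Inputs.** Minimum word length: 4 letters (section 16.0). Node threshold: above 0.5% (section 16.0). Cannabis labels: THC, CBD, marijuana, shatter (section 5.1). Generic terms: cannabis and nicotine (section 5.1). The protocol gives no derivation for the figure of four, so there is no calculation to reproduce.

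**Step 1: letter count against the rule (keep if at least 4).**

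| Term | Letters | Result |
|---|---|---|
| THC | 3 | excluded |
| CBD | 3 | excluded |
| shatter | 7 | kept |
| marijuana | 9 | kept |
| cannabis | 8 | kept |
| nicotine | 8 | kept |

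Two of the four cannabis labels are excluded. This counts labels, not how often each is used. Kept means only that the word passes the length filter; it must still exceed 0.5% to become a node.

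**Step 2: can a later step bring the excluded words back?**

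- The node rule acts on words with a frequency weighting, and a word outside the query has none.
- The grouping rule is limited to words above 0.5%, so it cannot attach THC or CBD to a cannabis node.
- The matrix step starts from this output.
- The urine screen in section 7.0 includes cannabis, but it indicates use and not what was vaped.

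**Step 3: size of the undercount.** Let M be the number of cannabis mentions in the transcripts and s the share voiced as THC or CBD. The query sees M × (1 − s), so the relative undercount is [M − M × (1 − s)] / M = s. The documents do not give s. Assumed values, per 100 cannabis mentions:

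| s (assumed) | Mentions seen | Undercount |
|---|---|---|
| 10% | 90 | 10% |
| 25% | 75 | 25% |
| 50% | 50 | 50% |
| 75% | 25 | 75% |

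At s = 0 nothing is lost. For any s above 0 the error is downward.

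**Step 4: does a change repair it?** With a minimum of three letters, or with THC and CBD mapped to a cannabis term before the query, all four labels enter the query. Nicotine is kept either way.

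**The case against.** The case for leaving the rule alone has real content:

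- The transcripts keep every word, and section 16.0 presents the query as a help in finding initial patterns.
- Section 16.0 defines a node by theme as well as by word, so a coder might still place a THC passage under a cannabis theme.
- The primary aim concerns how participants see vaping and why they vape. Section 10.0 says there is no structural outcome, and nothing in the protocol proposes to estimate the prevalence of cannabis vaping from word counts.
- The interview guide and case report form are not shown, so a structured question on substance cannot be ruled out.
- The labels in section 5.1 come from free-text answers in another dataset, not from telephone transcripts.

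These points limit the consequence but do not remove the defect. The grouping sentence covers only words above 0.5%, no other coding route is set out, and the protocol text describes no structured item on substance vaped.

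Some stronger readings are tempting, but the documents do not support them:

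- **Negation.** A reader might infer that dropping no and not would turn a statement that vaping is not safer into one that it is safer. A query of single words counts safer the same whether or not the negating word is also counted, so the length rule does not cause this and a shorter minimum would not cure it.
- **A distorted cannabis-to-nicotine ratio.** Section 5.1 also reports "74% of participants vaping nicotine", and a reader might apply an assumed loss to 33% against 74%. Those are shares of participants, whereas the query counts words and the matrix counts coded references.
- **Nicotine loses nothing.** This holds for the word nicotine. Short informal terms for nicotine would be dropped too, although the documents name none.
- **Cannabis disappears.** It does not: three of the cannabis terms in section 5.1 pass the filter.

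**Conclusion.** The point holds in a limited form. As written, the length rule bars THC and CBD from the query, and so from the nodes and matrices. Cannabis mentions are undercounted by the share voiced in those two words, and the two products cannot be reported separately. The exclusion follows from the protocol's text alone. That the undercount is more than zero rests on one assumption: that participants in this study use these terms, as people in the team's earlier cohort did. Its size cannot be fixed from the documents, and neither can the net effect relative to nicotine.

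This should be fixed before coding, but it does not undermine the study. It is a setting in an exploratory text step and no stated estimand depends on it. It does, however, affect the only analysis described for the interviews, on a topic named in the secondary objective.

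**What to change.** Amend section 16.0 in one of two ways:

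1. Lower the minimum to three letters and remove uninformative words with a stop-word list.
2. Keep four letters, but before the query recode THC and CBD to a cannabis node, preferably as distinct sub-nodes, from a synonym list fixed in advance.

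The second changes less. A minimum of two letters would go further than the defect requires and would admit many more function words.

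**Cost.** One sentence and a short list, with no new data. With the first option there is one detail to settle. Section 16.0 does not say what the 0.5% is a percentage of. If it is a share of the words counted, admitting three-letter words enlarges the denominator and changes which words become nodes, so the stop-word list should be applied before the threshold.

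### The only analysis described for the interviews ends in counts of topics and has no step that codes a mention as a reason for vaping, a perceived benefit or a perceived harm

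*Protocol*

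**What the plan says.** Section 6.1 sets the primary objective: "understand the perceptions and motivations for vaping in the OUD population receiving medication assisted treatment". Section 7.0 lists what the interviews are to bring out: "reasons for vaping, type of substance, effect of vaping on health". Section 10.0 fixes no primary measure. Because the information is open-ended, "there is no structural outcome".

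Section 16.0 then gives one analysis for the interview text, to be run in NVivo:

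1. "The free-text data will be run through a word frequency query to logically arrange the information and determine the most common words". Its purpose is stated modestly: "The word count query will help identify initial patterns in the data".
2. A length filter, offered as a protection of context: "the minimum number of letters permissible in the word frequency query will be set to four".
3. Each word above 0.5% of the text becomes a node. Words above that threshold with a common theme share one node. A node is defined as the set of text references belonging to a word or theme.
4. Matrix coding queries are run on the nodes: "The output of a matrix coding query is a chart that displays the number of references coded at each node", together with participants' demographic attributes.

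The thematic results are to be shown overall and split by age, ethnicity, sex, gender and type of medication assisted treatment.

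**The concern.** The objective asks two things about each topic: whether it is a motive, and how the participant judges it. The specified output records only how often the topic was mentioned. Someone who vapes to calm anxiety, someone whose anxiety got worse with vaping, and someone who noticed no effect can each add one reference to the same anxiety node. A smoking node would likewise mix those who vape in order to quit with those who vape and still smoke.

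At stake is how the main chart is read. A large health-related node could be taken as a common reason for vaping or as a common complaint, and the chart does not say which. In the subgroup displays, equal counts at a node could be taken as similar views when the views differ.

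**Working it through.** The protocol gives no figure to reproduce on this point. The check traces the steps of section 16.0, with two small calculations.

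**Objective against steps.** What each step of section 16.0 keeps:

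| Step | Keeps | Records role (reason, benefit, harm)? |
|---|---|---|
| Word frequency query | counts of words of four or more letters | no |
| Node rule (above 0.5%) | frequent words | no |
| Grouping | topics | no; grouping is by theme |
| Matrix query | references per node by attribute | no; crossed only with participant attributes |

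No later step that reads or codes the references for meaning is described.

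**What a node count identifies.** Write the references at a node as N = R + B + H + O (reasons, perceived benefits, perceived harms, other). The chart reports N; the objective needs the parts. As an illustration, 500 references could be 500 reasons and 0 harms, 250 and 250, or 0 and 500. In each case N = 500.

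Is a node of that size compatible with the 0.5% rule? Assume one mention per reference and a percentage taken over all words. A single word with 500 mentions then qualifies if the interviews together hold fewer than 500 / 0.005 = 100,000 words, which is 100,000 / 50 = 2,000 words for each of the 50 participants. The protocol gives no interview length. Over an assumed range of 500 to 4,000 words per interview, the threshold is:

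- 500 words: 50 × 500 × 0.005 = 125 mentions, or 2.5 per participant
- 1,000 words: 250 mentions, or 5 per participant
- 2,000 words: 500 mentions, or 10 per participant
- 4,000 words: 1,000 mentions, or 20 per participant

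Nodes are thus selected by volume of talk. The identity for N holds whatever the interview length.

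**What the length filter removes.** Invented sentences were passed through a count of words with at least four letters:

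- 'vaping does help anxiety' and 'vaping does not help anxiety' both give vaping 1, does 1, help 1, anxiety 1.
- 'vaping is bad, makes anxiety' and 'vaping is fun, makes anxiety' both give vaping 1, makes 1, anxiety 1.
- 'anxiety makes me vape' and 'vape makes me have anxiety' differ only by the incidental word 'have'. The anxiety count is 1 in both.

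The first two pairs match because the word that carries the judgement has three letters. Longer words such as 'worse', 'calm' and 'never' pass the filter, but no step ties them to the topic they qualify.

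**The case against.** The best defence is that section 16.0 describes a starting point. The word count is said to find initial patterns, grouping words into themes takes judgement, the results are called thematic, and a node holds retrievable text as well as a tally. The quoted sentence says what one query produces; it does not say the chart is the only result. The interview guide, with eight open questions, is an appendix that is not shown. If it asks about reasons and effects separately, a reference's role could be recovered from the question answered. A codebook might also sit in an analysis plan that is not shown.

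Much of this stands, and it rules out several stronger readings that a reader might infer:

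- *The study cannot answer its question.* Not supported. Interviews are transcribed, recordings are kept for 10 years, and nodes retain their text.
- *The node count is the declared primary measure.* Section 10.0 declares none. The count is only the one output described for the primary objective.
- *Groups with opposite views would give identical charts.* Not shown. Words of judgement with four or more letters can differ in frequency and form their own nodes. Only the count at the topic's own node can coincide.
- *The background predicts opposite opinions.* Section 5.1 calls the link between vaping and mental health probably bidirectional, but this concerns which comes first. It shows that one topic may be a cause or a consequence, not that participants will disagree about benefit and harm.

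The defence does not supply the missing step. Section 16.0 does not leave the method open: it fixes the software, length filter, threshold, grouping rule and output. It makes no use of the interview questions in coding, and the step after forming nodes is the matrix query.

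**Conclusion.** The point holds as a mismatch between objective and specified output. Followed as written, section 16.0 yields topic counts by demographic attribute. These do not separate reasons for vaping from perceived benefits and harms, and that separation is what section 6.1 asks for. The length filter adds to the problem in the frequency query by removing short negations and judgements, although it is justified as preserving context.

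The size cannot be given as a number. It depends on how mixed the views at each node are, and the protocol holds no data on that. The examples above show only that a node count does not determine the split. The conclusion assumes that section 16.0 is the whole of the planned interview analysis, as nothing else is described. The defect can be repaired without new data collection, so this is a change that should be made before analysis and does not undermine the study.

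**What to change.** In section 16.0, state that before the matrix query each reference at a node will be read in its surrounding text and given one code: reason for vaping, perceived benefit, perceived harm, or other (including neutral and denied). Report participants and references per code as the main result for the whole sample. Present the demographic breakdowns as descriptive, and keep the word-frequency counts as exploratory support. Setting the codes before analysis also avoids choosing categories after seeing the results.

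A single four-way code is preferable to a full grid of role by direction. Three roles by three directions would give 3 × 3 = 9 cells per node, and splitting these by five attributes in 50 people would leave many nearly empty.

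The cost is extra coding time on up to 50 transcripts within the planned NVivo project. Some references will be ambiguous and fall into the last category, and subgroup cells will still be sparse.
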